#### Pain catastrophising using the pain catastrophising scale

The Pain Catastrophising Scale measures the tendency to ruminate about pain, magnify pain, and feel helpless about pain. All 13 items are measured on a 5-point Likert scale (where 0 = low levels of catastrophising and 4 = high levels of catastrophising). The highest possible total score of 52 indicates the greatest level of catastrophising. It has high internal consistency and is associated with heightened pain, psychological distress, and physical disability [64].

#### Use of coping skills to manage pain using the coping attempts scale of the Coping Strategies Questionnaire (CSQ)

The CSQ [65] can be used to measure how often a patient uses six cognitive and behavioural pain coping strategies to manage pain (diverting attention, reinterpreting pain sensations, coping self-statements, ignoring pain sensations, praying and hoping, and increasing activity level). Items are measured on a 7-point Likert scale (where 0 = never uses coping skills and 7 = always uses coping skills). Based on prior factor analyses of this instrument [66], participant’s responses will be converted to scores on the Coping Attempts factor of the CSQ. The CSQ has demonstrated sensitivity to change from treatment in chronic pain samples as well as good internal consistency and construct validity [66].

### Other measures

#### Treatment adherence

The number of Skype physiotherapy sessions attended by each participant will be recorded by the treating physiotherapist and submitted to the researchers using scheduled online treatment notes. The number of PainCOACH sessions completed will be automatically recorded by the program progress log which will be monitored regularly by the researchers. During the intervention period, adherence to the home exercise program will be self-reported in weekly log books, which at the completion of the intervention will either be transcribed to an online survey or returned by post, depending on participant preference. Pain coping skills practice and coping confidence (self-efficacy for using pain coping skills to manage pain) will be recorded using the PainCOACH practice tracking log (COACHtrack) or alternatively by completing weekly logs that will either be transcribed to an online survey or returned by post.

Participants in the PCST + Ex group will also rate their adherence to their home exercise program over the previous 3 months (from ‘not at all’ to ‘completely as instructed’) at 3, 6 and 9 months using an online 11-point NRS. They will also report the number of exercise sessions they completed and how often they used the PainCOACH skills in the previous 2 weeks, at 3, 6, and 9 months. Participants in both groups will report which online education information sheets were accessed in the past 3 months 3, 6, and 9 months using an online checklist.

#### Adverse events and use of health services/co-interventions

Adverse events will be defined as any health problems that participants: i) believed to be caused by the treatment; ii) that required them to see a health professional or take medications; iii) and/or that interfered with function for 2 or more days. Information on adverse events throughout the 13 week intervention will be collected for the combined group via exercise log books and at 3, 6 and 9 months for both groups via an online survey. Participants’ use of health services and co-interventions (medication for knee pain and any other treatment for knee pain) will be collected via an online survey at 0, 3 and 9 months. Direct health care costs and direct non-health care resources will be collected at the 9 months via an online survey.

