### Procedure

Figure 1 outlines the trial phases. Eligibility of volunteers will be initially confirmed via an online screening survey followed by a telephone interview. Baseline, 3-month (primary time point) and 9-month (secondary time point) assessments will be conducted via the Internet using online assessment surveys. Additionally, participants will complete log books to capture adherence and adverse event data. These will be either transcribed by participants to an online survey or mailed back to researchers, as preferred by each participant. Ethical approval has been obtained from the University of Melbourne Human Research Ethics Committee (No. 1339459). All participants will provide written informed consent. For participants with bilaterally eligible knees, only the most painful knee (as identified by the participant) will be evaluated.

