### Randomisation and allocation concealment

On completion of baseline assessment, participants will be consecutively randomised to one of two groups: 1) educational control (online educational material) or 2) intervention group (online educational material, Internet-based PCST and physiotherapy-guided exercise program delivered via the Internet). Computer generated randomisation will be conducted by random permuted blocks of size 2-8 stratified by gender (male or female) and residency (metropolitan or rural), prepared by our study biostatistician (MS). To conceal randomization, consecutively numbered, sealed, opaque envelopes will be prepared by a researcher with no other involvement in the study. The envelopes will be stored in a locked location and will be opened in sequence within each stratum to reveal group allocation.

All primary and secondary outcome data will be completed online and thus will be automatically entered into a database. By necessity, participants and physiotherapists will be unblinded to group allocation; however, participants will remain blinded to research hypotheses. The statistician will be blinded to group allocation until completion of the statistical analyses.

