**5. Others (1 exercise if appropriate)**			
**Knee ROM**	Weight bearing	A. Deep squats holding onto a bench/chair	**Progression:** increase squat depth
**Hip ROM**	Weight bearing	B. Deep lunges holding onto back of chair/bench	**Progression:** increase lunge depth
**Hip extensors**	Weight-bearing	C. Bridging	**Progression:** split leg bridge, single bridge with a hold, bridging one leg

Using the Internet to mediate learning, the physiotherapist will begin each participant’s exercise program by selecting exercises and prescribing dosages based on findings from an initial assessment of the participant’s pain and perceived level of effort during performance of an exercise. The participant will learn each exercise by observing as the physiotherapist demonstrates the exercise and then performing it under the physiotherapist’s supervision.

The physiotherapist will perform a brief assessment at each physiotherapy session to ascertain any adverse effects that may have occurred with home exercises and check quality and form of exercise performance. Progression of exercises will be provided by varying the type of exercise as well as the number of repetitions, load or degree of difficulty within an exercise. The prescribed resistance will aim to approximate a 10-repetition maximum level and a patient-rated level of effort experienced during each strengthening exercise of at least 5 out of 10 (hard) on a modified Borg Rating of Perceived Exertion CR-10 scale designed specifically for strengthening exercise [51].

In order to minimise burden of exercise, only the study knee will be the focus of treatment and evaluation. If participants have bilateral symptoms, the physiotherapist may choose exercises that are performed in weight-bearing on both legs simultaneously to achieve bilateral strength gains within the constraints of the treatment protocol.

Although some discomfort is expected during the exercise intervention, any exercise-related pain should subside to usual levels by the next day with no increase in knee swelling following the exercise session. Participants will be taught how to determine whether pain levels are acceptable or not during and for a short time after the exercises. If a specific exercise is aggravating the participant’s pain, then the physiotherapist will reduce the resistance, dosage and/or level of challenge within the exercise until the pain flare settles or change the exercise completely if it remains pain provoking.

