#### Treatment fidelity

Eight experienced musculoskeletal physiotherapists (4 female, 4 male) in 7 locations around metropolitan Melbourne and regional Victoria have been selected and trained to deliver the study exercise intervention. They have an average of 16 years (minimum 3 years, maximum 28 years) of clinical experience treating musculoskeletal disorders. They attended a full-day training course in Melbourne conducted by the researchers on February 22nd 2014 and were provided with a detailed intervention manual. Training included information about study procedures and protocol, exercise delivery, progression and monitoring. As therapists are encouraged to support and reinforce pain coping skills taught on PainCOACH, they also received background information, exposure and education about those skills so they can be integrated into the exercise program and daily life. Regular telephone/Skype meetings between the physiotherapists and a member of the research team will be held throughout the study. Physiotherapists will complete standardised treatment notes for each participant’s individual treatment session and return these via an online survey within 48 hours of the session appointment. Treatment fidelity will be assessed using a treatment check list applied to key points within the treatment notes.

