**Other measures**		
Adherence to intervention	Number of physiotherapy sessions attended	During intervention
	Weekly home exercise log books	During intervention
	PainCOACH module completion	During intervention
	PainCOACH practice via COACHTrack/ log books	During intervention
	Home exercises - 11-point numeric rating scale	3, 6 and 9 months
	Frequency of home exercise sessions previous 2 weeks	3, 6 and 9 months
	Frequency of pain coping skills in previous 2 weeks	3, 6 and 9 months
	Educational material accessed in previous 3 months	3, 6 and 9 months
Adverse events and harms	Questionnaire	3, 6 and 9 months
Health cost data	Questionnaire	9 months
Descriptive information	Questionnaire	0 months
Medications and co-interventions	Questionnaire	0, 3, 9 months
Treatment benefit expectations	5-point ordinal scale	0 months

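### Adverse events have an extra recording source (log books) in PCST + Ex only, so a between-group count that pools sources would overstate harms in that arm

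*Protocol article*

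**What the plan says.** The Protocol article describes adverse-event capture in three places, and they do not agree.

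- **Adverse events and use of health services/co-interventions:** "Information on adverse events throughout the 13 week intervention will be collected for the combined group via exercise log books". The sentence then adds a second source, which the two arms share: "at 3, 6 and 9 months for both groups via an online survey". Because the second part is for both groups and the logs are exercise logs, the combined group must mean PCST + Ex.
- **Procedure:** "participants will complete log books to capture adherence and adverse event data", with no restriction to one arm.
- **Table 3, Other measures:** the row "Adverse events and harms" lists only a questionnaire at 3, 6 and 9 months.

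The adverse-events section defines an event by three criteria: (i) "believed to be caused by the treatment", (ii) a need for professional care or medication, and (iii) limited function for at least two days. The last is joined by an and/or.

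Three further statements bear on the point. Under Randomisation and allocation concealment, "participants and physiotherapists will be unblinded to group allocation". The exercise-delivery text after Table 2 says: "The physiotherapist will perform a brief assessment at each physiotherapy session to ascertain any adverse effects that may have occurred with home exercises". Under Treatment fidelity, physiotherapists write session notes and "return these via an online survey within 48 hours of the session appointment". The stated uses of those notes are fidelity and, under Treatment adherence, attendance.

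**The concern.** A health problem in the first 13 weeks has two chances of being recorded in PCST + Ex, in the log book and in the 3-month survey. In the control arm it has one. If events from both sources go into one between-group table, PCST + Ex will show more events even when the true incidence is the same, and exercise will look less safe than education because it was watched more closely.

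The definition may add to this. An exerciser can readily blame a new problem on the programme. A control participant, who knows the allocation and has only information sheets, can hardly do so. If believed causation is required, the two arms face different thresholds for the same problem.

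Harms are listed for both groups, and the Discussion hopes to guide clinical practice, so the harms comparison is likely to be read. The primary outcomes and the sample size do not depend on it.

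**Working it through.** The document states no adverse-event rate or detection rate, so there is no figure of its own to reproduce. The check has three parts.

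**1. Sources by arm (from the adverse-events section)**

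| Period | PCST + Ex | Control |
|---|---|---|
| Intervention (13 weeks) | Log book + 3-month survey | 3-month survey |
| After intervention | 6- and 9-month surveys | 6- and 9-month surveys |

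The imbalance is confined to the intervention period.

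**2. Size if the sources are pooled**

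Assumptions, none from the document:
- true incidence is equal in both arms;
- the survey detects a share s of events in either arm;
- the log book, independently, detects a share l;
- each event is counted once.

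Detected share in PCST + Ex: 1 − (1 − s)(1 − l). Detected share in control: s.

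Apparent ratio r = [1 − (1 − s)(1 − l)] / s

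| s | l = 0.3 | l = 0.5 | l = 0.8 |
|---|---|---|---|
| 0.5 | 1.30 | 1.50 | 1.80 |
| 0.6 | 1.20 | 1.33 | 1.53 |
| 0.7 | 1.13 | 1.21 | 1.34 |
| 0.9 | 1.03 | 1.06 | 1.09 |

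Example with an assumed true risk of 30%, s = 0.7 and l = 0.5: PCST + Ex shows 0.30 × 0.85 = 25.5%, control shows 0.30 × 0.70 = 21.0%, and r = 25.5/21.0 = 1.21.

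Over the full 9 months, with a constant event rate and the same s throughout, only the first third is affected, so the ratio is (r + 2)/3. For r = 1.2 this is 3.2/3 = 1.07; for r = 1.8 it is 3.8/3 = 1.27.

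If the comparison uses only the common survey, both arms detect s and the expected ratio is s/s = 1.00.

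**3. The definition, read two ways**

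- *Criterion i required, plus ii and/or iii:* a control participant's problem counts only if attributed to the reading material. The definition is then asymmetric even on the common survey.
- *Any one criterion suffices:* a control participant qualifies through ii or iii without naming a cause. Criterion i alone could still add events, more plausibly in the exercise arm.

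The wording does not settle which reading applies.

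**The case against.** A reader might infer that every between-group comparison of harms is biased and that the trial cannot tell real harm from closer recording. The document does not support that. The sentence that introduces the log books also gives both arms one survey on one schedule, and Table 3 lists only a questionnaire. A comparison limited to the survey has the same instrument in each arm.

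A reader might also count the seven physiotherapy sessions as a further adverse-event source. They are described as a clinical review of home exercise. The adverse-events section does not name them, and the stated uses of the session notes lie elsewhere. Any contribution to the harms record is inferred, and the calculation gives them no weight.

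Third, the bias requires pooling. Data and statistical analysis neither states pooling nor specifies a harms test, and the choice of source may properly sit in an analysis plan that is not shown. That silence is not held against the document. What remains is what it does state: unequal collection, a definition open to two readings, and three descriptions of the sources that do not match.

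Finally, the ratios rest on assumed rates. Independence is doubtful, because the same person fills in both sources and log books are transcribed or posted at the end of the intervention, close to the 3-month survey. Positive correlation would lower the ratio, and a highly sensitive survey nearly removes it. These limits stand.

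**Conclusion.** The point holds in a limited form. Collection during the intervention is unequal by design, and a table that pools log-book and survey events would overstate harms in PCST + Ex at equal true incidence. Under independent detection the intervention-period ratio is 1.2 to 1.8 for survey sensitivity of 50–70% with log-book sensitivity of 50–80%. It is about 1.03 to 1.09 at 90% survey sensitivity with log-book sensitivity of 30–80%. Over 9 months, 1.2 to 1.8 shrinks to about 1.07 to 1.27 if the event rate is constant. The direction under pooling is firm; the size is illustrative.

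The asymmetry in the definition is conditional on criterion i being mandatory, and its size cannot be estimated from the document. The point is worth acting on because the remedy is cheap, but efficacy conclusions do not turn on it.

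**What to change.** 1. State that the between-group adverse-event comparison uses only the 3-, 6- and 9-month surveys that both arms complete.
2. Report log-book events, and any events detected at sessions, separately and descriptively for PCST + Ex.
3. Reword the definition so that every health problem meeting criterion ii or iii is counted whatever its believed cause, and record attribution to treatment as a separate field.
4. Align Procedure, Table 3 and the adverse-events section on who keeps adverse-event logs.

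**Cost:** a reworded definition, one survey item for attribution and a changed table shell. Step 1 uses data the plan already collects. Recruitment began in March 2014, so surveys completed before the change might lack the attribution item, and the report should say so.

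**Downside:** the comparative table will show fewer PCST + Ex events than the pooled sources would, although the remainder are still reported. Keeping a weekly log may also sharpen recall at the survey in one arm. The survey-only comparison does not remove that difference, and it cannot be quantified from the document.

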#### PCST + Ex condition

Participants in the PCST + Ex group will receive three inter-related interventions that are delivered via the Internet. First, they will receive the same specific URL-link to access the same online educational material as the educational control group. Second, they will receive access to PainCOACH, which includes eight 35- to 45-minute modules that each teach a pain coping skill shown to help people manage persistent OA pain. The modules are designed to be completed at the rate of one per week. Participants will also receive seven physiotherapy consultations delivered over the Internet using a video telephony service, Skype™. The initial session will be 45-minutes, followed by 30-minute sessions thereafter. During these consultations, participants will be prescribed an individualised home-based exercise program to be performed three times weekly. The weekly PainCOACH sessions will occur during the 3-month intervention period in Weeks 1-8, with a booster session at Week 11. The physiotherapy sessions will occur in Weeks 2, 3, 4, 6, 8, 10 and 12 of the 3-month intervention period. Participants will receive further monthly PainCOACH boosters during the 6 months following the intervention period, where they will be encouraged to review the final module of the program as well as revisit useful/meaningful modules. They will also receive monthly email reminders to encourage them to continue their exercises at home and practice their pain coping skills.

Prior to beginning the intervention, participants will receive Skype set-up training, including instructions on how to set up their web-camera and their exercise environment. They will also be given an instructional manual and password access to PainCOACH from the researchers. Any equipment required for the exercises (e.g. elastic bands, ankle weights, web camera if required, and pedometer if required) will be mailed to participants before the intervention commences.

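### Adverse events are collected from log books plus survey in PCST + Ex but from the survey alone in controls, so a between-arm comparison that pools sources would tend to overstate harm in PCST + Ex

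*Protocol article*

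**What the plan says.** The section on adverse events and use of health services in the Protocol article sets the collection rule. Events during the 13-week intervention are "collected for the combined group via exercise log books and at 3, 6 and 9 months for both groups via an online survey". Table 3 lists the adverse-event instrument as a questionnaire at 3, 6 and 9 months and lists log books only under adherence.

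The Treatment adherence section gives the frequency of the exercise record: "adherence to the home exercise program will be self-reported in weekly log books". Both kinds of log it describes (home exercise and pain coping practice) belong to components that only PCST + Ex receives.

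The Procedure section is less specific. It says that "participants will complete log books to capture adherence and adverse event data" and names no arm.

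The exercise text after Table 2 adds a further enquiry: "The physiotherapist will perform a brief assessment at each physiotherapy session to ascertain any adverse effects that may have occurred with home exercises". Only PCST + Ex has these sessions, and the intervention section schedules seven: "The physiotherapy sessions will occur in Weeks 2, 3, 4, 6, 8, 10 and 12 of the 3-month intervention period".

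The definition rests on the participant's own judgement. It begins "Adverse events will be defined as any health problems that participants: i) believed to be caused by the treatment" and goes on to events that led to care or medication or that limited function for at least 2 days. Reporting is open-label, since "participants and physiotherapists will be unblinded to group allocation".

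**The concern.** How many adverse events are counted depends on how often and how promptly people are asked. Here one arm can write an event down in the week it happens, and the other must remember it at the end of about 3 months. The definition admits minor, short-lived problems, such as taking medication or two days of reduced function. These are plausibly what a weekly record catches and a 3-month recall misses.

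If the sources are pooled, an excess in PCST + Ex could be real exercise-related harm or simply closer recording, and the data could not tell the two apart. The affected period is the intervention itself, which ends at the primary time point and is when exercise-related events are most relevant. The article gives no rule for combining log-book and survey events. If the source of each event is not recorded at entry, a later analysis plan may not be able to separate them.

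**Working it through.** **Step 1: sources by arm, as the article states them.**

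| Source | PCST + Ex | Control |
|---|---|---|
| Exercise log book, intervention period | yes, weekly | none described |
| Online survey at 3, 6 and 9 months | yes | yes |
| Physiotherapist enquiry at 7 sessions | yes, but not named as an adverse-event data source | none |

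Counting only the sources that the adverse-event section names, PCST + Ex has up to 13 weekly log entries plus 1 survey in the first 3 months, and controls have 1 survey. After 3 months the described sources are the same in both arms.

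**Step 2: is there a stated figure to reproduce?** No. The article gives no expected adverse-event rate, no capture rate and no planned adverse-event comparison. What follows is an illustration under assumptions.

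**Step 3: a simple model.** Assumed inputs:
- p: true risk of an event, equal in both arms.
- s: probability that the survey captures an event, equal in both arms because the survey is shared.
- e: share of survey-missed events that the extra source recovers in PCST + Ex.

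Recorded risk in controls = p × s.
Recorded risk in PCST + Ex = p × [s + (1 − s) × e].
Apparent risk ratio = 1 + e(1 − s)/s, which does not depend on p.

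| s | e = 0.3 | e = 0.6 |
|---|---|---|
| 0.9 | 1 + 0.3 × 0.1/0.9 = 1.03 | 1 + 0.6 × 0.1/0.9 = 1.07 |
| 0.7 | 1 + 0.3 × 0.3/0.7 = 1.13 | 1 + 0.6 × 0.3/0.7 = 1.26 |
| 0.5 | 1 + 0.3 × 0.5/0.5 = 1.30 | 1 + 0.6 × 0.5/0.5 = 1.60 |

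In absolute terms, with p = 20%, s = 0.5 and e = 0.6, the recorded risks are 0.20 × 0.80 = 16% and 0.20 × 0.50 = 10%. With 74 per arm that is about 11.8 against 7.4 participants, with no true difference.

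Because e is defined among events the survey missed, the model does not need log and survey capture to be independent. If the same people forget to use both, e is simply smaller.

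**Step 4: direction.** For any s below 1 and e above 0, the ratio exceeds 1. The direction is therefore fixed by the collection rule, and only the size is assumed.

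**Step 5: survey-only comparison.** Setting e = 0 gives a ratio of 1.00 when true risk and survey capture are equal across arms.

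**The case against.** The strongest case on the other side has four parts.

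First, both arms complete an adverse-event survey at the same three times, so a fair comparison is available. This stands. A reader might infer that every between-arm comparison of harm is biased by this collection scheme. The article does not support that, because a survey-only comparison is free of the source imbalance.

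Second, no such comparison is announced. Adverse events are absent from the hypotheses, the primary endpoints and the analysis section, and Table 3 files them under other measures. The rules for combining sources are the sort of detail left to an analysis plan that is not shown. This stands in part. It cannot be said that the trial will report excess harm, only that pooling would tend to produce it. But the point does not rest on an omission alone, because unequal collection is itself a stated rule of the article.

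Third, a reader might count the seven physiotherapist enquiries as a further adverse-event source. The adverse-event section and Table 3 do not list them. The stated uses of the physiotherapists' notes are attendance and fidelity; for the latter, "Treatment fidelity will be assessed using a treatment check list applied to key points within the treatment notes". The enquiries may add to the imbalance, but that is an inference, and the log books carry the point without them.

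Fourth, closer monitoring of the arm that exercises is a defensible safety choice, and controls have no prescribed programme to log. This also stands. The problem lies in comparing the resulting counts, not in collecting them.

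**Conclusion.** The concern holds in a limited form. During the 13-week intervention, ascertainment is unequal by design, and a between-arm comparison that pools all sources would tend to overstate harm in PCST + Ex. The direction follows from the article's own collection rule. The size does not: the range of about 1.03 to 1.6 for the apparent risk ratio rests wholly on assumed survey capture of 0.5 to 0.9 and assumed recovery of 30% to 60% of missed events. If survey capture is high, the distortion is small.

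The Procedure section and the adverse-event section also differ on who keeps log books. The adverse-event section is the more specific, but someone reading the Procedure section alone would think ascertainment was equal.

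The primary and secondary efficacy outcomes are not affected. The change should be made because it is cheap and protects the interpretation of the safety data.

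**What to change.** 1. In the adverse-event section or the analysis section, state that between-arm comparisons of adverse events use only events reported in the common 3-, 6- and 9-month online survey.
2. Record the source of each event. Log books may themselves be transcribed into an online survey, so the flag must separate a transcribed log entry from an answer to the common survey.
3. Tabulate log-book events, and any that physiotherapists elicit, separately as descriptive safety data for PCST + Ex.
4. Reconcile the Procedure section with the adverse-event section on which arm completes adverse-event log books.

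The cost is a few sentences and one data field, with no new participants, visits or questionnaires. No safety data are discarded. The downside is that the comparison rests on survey-reported events only. Some bias may also remain: reporting is open-label, and keeping a log or being asked by a physiotherapist may improve recall at the 3-month survey. An equivalent adverse-event log in controls would be an alternative, but it adds burden in an arm otherwise left to use the material at its own pace.
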